### **Data analysis**

The primary outcome will be compared between each of the study arms using methods appropriate for cluster randomized trials. Due to the small number of clusters per arm analysis based on cluster-level summaries will be applied. Point estimates of the primary outcome will be calculated using the weighted average of the cluster proportions, with the weights provided by the sample size for each cluster. If the distribution of the summary measures in each study arm is skewed, a logarithmic transformation to the proportions will be considered. An overall estimate of the risk difference will be obtained by taking a weighted average of the stratum-specific estimates with the weights proportional to the number of clusters in each stratum since an equal number of clusters have been allocated to the study arms within each stratum. 95% confidence intervals (CI) will be adjusted for observed between-cluster variance and formal hypothesis testing will be conducted using stratified t-tests. Adjustment for covariates, including patient and provider characteristics and knowledge, contextual factors, and process factors, will be carried out using a two-stage process. In the first stage a logistic regression model including stratum as a fixed effect and the covariates of interest, but excluding the intervention effect, will be fitted to calculate cluster-specific expected values. The difference of observed to expected values will give the

[figure not shown]

difference-residual for each cluster. In the second stage, the above methods are carried out with the cluster-level proportions replaced with the covariate-adjusted residuals.

Secondary outcomes will be analyzed using the methods described above. To examine whether secondary outcomes associated with the patient vary according to urban/rural residence and socioeconomic status methods appropriate for examining an interaction between the intervention and the individual-level variable will be applied [43].

Data will be double entered using Microsoft Access 2007 (Microsoft Inc., Redmond, WA, USA) and analyzed using STATA version 11.0 (STATA Corporation, College Station, TX, USA). A full analysis plan will be reviewed and agreed before the data are analyzed.

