#### ***Provider training intervention (including support visits)***

In addition to the supply of RDTs and the demonstration of how to use RDTs, facilities in clusters randomized to arms 2 and 3 will receive additional provider training and support visits. Provider training on malaria diagnosis and treatment will be conducted over 2 days and contains six training modules on: (1) Knowledge on malaria; (2) Introduction of the updated guidelines for malaria diagnosis and treatment; (3) Appropriate diagnosis; (4) Appropriate treatment when test is positive; (5) Appropriate treatment when test is negative; and (6)

Effective communication. Together these training modules will improve providers' knowledge and skills on why it is important to test for malaria, how to use a RDT, and the effective implementation of clinical guidelines. The first module describes the current burden of malaria in Nigeria, in addition to its causes, signs, and symptoms. The second module reviews the clinical guidelines and highlights the importance of malaria testing in febrile patients before treatment is prescribed. The module on appropriate diagnosis includes a practical session in which all providers will get hands-on experience of the steps involved in using an RDT. This is equivalent to the intervention 'demonstration on how to use RDTs' that is delivered to participants in Arm 1. Module 4 provides training on what treatment to give when a test is positive, the recommended types of antimalarial drugs, including the dosage regimens for different age groups and types of ACT. Module 5 provides advice on other causes of febrile illness which should be investigated if the malaria test is negative. The objective of the last module on communication is to improve health provider knowledge of the importance of patient communication and barriers to effective communication. Providers will learn how to discuss different treatment options with patients especially when the test result is negative.

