## Hypotheses

1. The provider intervention will be more effective and cost-effective in improving the treatment and diagnosis of malaria compared to what is expected to be standard practice.

The components of the provider intervention will lead to the delivery of more appropriate treatment. Specifically, the provider intervention will improve the competency of providers to deliver treatment to febrile patients based on the result of a malaria test.

2. The combined provider and school-based intervention will be more effective but also more costly compared to expected standard practice and the provider intervention alone.

The school-based intervention will have a direct effect by improving the knowledge of community members in terms of why they should be tested, the availability of testing, and that ACTs are recommended for confirmed cases of malaria. We expect that these changes in knowledge will also affect what patients ask for when they attend health facilities, and are therefore more likely to ask for a test and/or ask for an ACT. The school-based component of the community intervention will also have an indirect positive effect

on provider practices. Specifically, if providers are aware of the school-based intervention, they will know that patients have been made aware that malaria testing is available and recommended, and that malaria should be treated with an ACT. It is hypothesized that the providers will then feel more comfortable suggesting that patients are tested and confident in recommending that confirmed cases should be given an ACT. While the combined interventions are predicted to have a positive synergistic effect, the combined costs of a school-based intervention in both primary and secondary schools and of provider training workshops that involve supervisory visits are likely to be greater than those associated with expected standard practice or the provider intervention alone.

The relationship between the study hypotheses and outcomes are summarized in Figure 1.

Outcomes

Primary outcome

The primary outcome is the proportion of patients attending facilities that report a fever or suspected malaria and receive treatment according to malaria guidelines. The corresponding measure of cost-effectiveness is the cost per febrile patient that receives treatment according to the malaria guidelines.

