Treatment according to the malaria guidelines is a composite endpoint requiring that: febrile patients should be tested for malaria, using either microscopy or an RDT; the patient should receive an ACT if s/he has a positive malaria test result; and the patient should not receive an antimalarial if s/he has a negative malaria test result.

The outcome measure is summarized in Figure 2.

Secondary outcomes

Secondary outcomes include the following:

[figure not shown]

Figure 1 Effect of interventions on the treatment received by patients.

[figure not shown]

**Figure 2** Primary outcome measure.

1. Patients: proportion of febrile patients that are tested for malaria; proportion of febrile patients receiving an antimalarial that receive an ACT; proportion of febrile patients receiving an ACT that receive the correct dose for their age; proportion of febrile patients receiving an ACT that accurately report how to take the medicine; proportion of febrile patients that report they are satisfied with the care received; proportion of patients attending a health facility that report a school malaria event took place in their community.
2. Providers: proportion of providers that report they were satisfied with the training received; proportion of providers that report febrile patients should be tested for malaria; proportion of providers that know how to identify positive, negative, and invalid malaria RDT results; proportion of providers that know ACT should be given if the malaria test is positive and that an antimalarial should not be given if the malaria test is negative; proportion of providers that know the correct dose of the first line ACT in an adult and in a child aged 2 years.
3. Community members: proportion of individuals that were aware of a school malaria event; proportion of individuals that report they had attended school malaria event; proportion of individuals that report febrile patients should be tested for malaria; proportion of individuals that know ACT is the recommended treatment for malaria; proportion of individuals that know ACT should be given if the malaria test is positive and that an antimalarial should not be given if the malaria test is negative.

4. Costs: total cost of the provider and school-based interventions; mean cost per provider trained under the provider intervention; mean cost per school participating in the school-based intervention.

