### Evaluation design

The evaluation of the interventions will use data collected in a patient exit survey, a register of malaria tests conducted by the provider during patient consultations, a provider survey, documentation of the intervention process, a household survey, and costing of the intervention activities. The patient exit survey will be administered before the provider survey to ensure that the treatment received by patients is not influenced by the content of the provider questionnaire. Each of these research instruments is described below.

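### The covariate-adjusted analysis conditions on knowledge and process factors that arise after randomisation, so its risk difference is not the effect of the randomised intervention

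*Protocol*

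**What the plan says.** The protocol's Data analysis section first sets out an unadjusted analysis: cluster-level summaries, a weighted risk difference across strata, an interval based on the between-cluster variance, and "formal hypothesis testing will be conducted using stratified t-tests". It then adds: "Adjustment for covariates, including patient and provider characteristics and knowledge, contextual factors, and process factors, will be carried out using a two-stage process". In stage 1, a logistic model contains stratum and the covariates, "but excluding the intervention effect, will be fitted to calculate cluster-specific expected values". In stage 2, "the above methods are carried out with the cluster-level proportions replaced with the covariate-adjusted residuals".

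Elsewhere the protocol treats knowledge as something the interventions change:

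- **Provider training intervention:** the modules are meant to raise providers' "knowledge and skills on why it is important to test for malaria, how to use a RDT".
- **Hypotheses:** the first says that "the provider intervention will improve the competency of providers to deliver treatment to febrile patients based on the result of a malaria test". The second says that the school component works through what community members know, which then alters what patients request.
- **Secondary outcomes:** these include the "proportion of providers that know ACT should be given if the malaria test is positive", with a matching item for community members.

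Timing is also given. The exit survey starts three months after implementation, and its module F covers patient knowledge. The provider survey comes later: "The patient exit survey will be administered before the provider survey to ensure that the treatment received by patients is not influenced" by the provider questionnaire. Process data are recorded while the interventions are being implemented.

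**The concern.** A covariate can be adjusted for without changing the meaning of a randomised comparison if it was fixed before allocation or cannot be altered by it. The knowledge and process variables named here do not meet that condition. Knowledge is measured after the interventions and is their stated mechanism, so holding it constant removes the part of the effect that runs through it.

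Omitting the arm term from stage 1 adds a second loss. Any covariate that differs between arms because of the intervention takes up some of the arm difference in the fitted values, even if it has no influence on treatment. The residuals compared in stage 2 have already lost that part.

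The adjusted analysis has its own estimate, interval and test. A reader could take a smaller or non-significant adjusted result as evidence that the intervention effect is explained away by imbalance, when the analysis has in fact subtracted the intervention's own mechanism. The same methods are also extended to the secondary outcomes, so by the letter of the text a knowledge outcome could be adjusted for knowledge.

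**Working it through.** **Reproducing the plan's figure.** From Sample size (Patient exit survey): 50 patients per cluster (m), coefficient of variation 0.35 (k), 80% power, 5% significance (taken as two-sided), steps of 10% to 25% and 25% to 40%. Formula:

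c = 1 + (1.96 + 0.84)² × [p0(1−p0)/m + p1(1−p1)/m + k²(p0² + p1²)] / (p1−p0)²

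- 25% to 40%: the bracket is 0.00375 + 0.0048 + 0.02726 = 0.03581, and 7.849 × 0.03581 / 0.0225 = 12.49. Adding 1 gives 13.49, so 14 clusters per arm, as stated. Power at 14 is 81.5%.
- 10% to 25%: 5.03 + 1 = 6.03, so 7 would be enough.

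This calculation concerns the unadjusted comparison and is sound.

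**Expected result of the two-stage adjustment.** Take one binary covariate with prevalence q0 and q1 in two equal arms, a true difference D, and a share s of D carried by the covariate. Effects are taken as additive. With one binary covariate the logistic fit is saturated, so the pooled stage-1 slope is

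sD/(q1−q0) + (1−s)D × [(q1−q0)/4] / [q̄(1−q̄)], where q̄ = (q0+q1)/2.

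Subtracting slope × (q1−q0) from D leaves

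**adjusted difference = (1−s) × D × F, with F = 1 − (q1−q0)² / [4q̄(1−q̄)].**

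The factor (1−s) is the mediated part. F is the loss from omitting arm. If the covariate is balanced (q0 = q1) and carries none of the effect (s = 0), then F = 1 and the full D remains.

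**Numbers.** Knowledge figures come from Sample size (Provider survey; Household survey). The share s is not in the protocol and is varied. Household-survey community knowledge stands in for patient knowledge.

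- *Arm 3 vs arm 2*, community knowledge 20% vs 50%, D = 15: F = 1 − 0.09/0.91 = 0.901. At s = 0, 50 and 100% the adjusted difference is 13.5, 6.8 and 0 points.
- *Arm 3 vs arm 1*, community knowledge 10% vs 50%, D = 30: F = 1 − 0.16/0.84 = 0.810. The result is 24.3, 12.1 and 0 points.
- *Arm 2 vs arm 1*, provider knowledge 50% vs 75%, D = 15: F = 1 − 0.0625/0.9375 = 0.933. At s = 0, 25% and one third it is 14.0, 10.5 and 9.3 points. One third is the ceiling: with a 10% control rate and 50% knowledgeable, knowledge can add at most 0.10/0.50 = 0.20 to the success probability, and 0.20 × 25 points = 5 of the 15.
- *A process factor at 0% vs 90%* (an assumption, not a protocol figure), D = 15: F = 1 − 0.81/0.99 = 0.182, leaving 2.7 points or less. At 0% vs 100%, nothing is left.

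**Simulation** (1,000 runs, 14 clusters per arm, 50 patients each, k = 0.35, one stratum, t-test on cluster residuals):

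| Comparison | Share | Adjusted difference | Rejection rate |
|---|---|---|---|
| Arm 3 vs 2 | 0 | 13.2 | 73% |
| | 50% | 6.9 | 23% |
| | 100% | 0.0 | 2% |
| Arm 3 vs 1 | 0 | 24.2 | 100% |
| | 50% | 12.2 | 87% |
| | 100% | 0.0 | under 1% |
| Arm 2 vs 1 | 0 | 14.0 | near 100% |
| | 25% | 10.4 | 91% |
| | one third | 9.3 | 82% |

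A repeat run for arm 3 vs arm 2 gave power of about 72%, 24% and 3%. In the same runs the unadjusted arm 3 vs arm 2 test rejected in about 78 to 86% of trials. With two strata and an intracluster correlation of 0.25 for knowledge, arm 2 vs arm 1 gave 13.9 points with no mediation and 9.2 at one third (about 83% rejection).

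**The case against.** The strongest reply is that the trial's main test survives. The unadjusted risk difference, interval and t-test come first in Data analysis, the reference to formal testing belongs to them, and nothing says that the adjusted result replaces them. This stands, and it limits the point to a secondary estimate and how it will be read.

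Second, a full analysis plan is announced and may narrow the covariates. It may. But the protocol itself names knowledge and process factors, so a plan that follows it carries the problem forward.

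Third, baseline knowledge might be meant, since the provider sample-size text mentions a baseline survey. Data analysis does not say so, and process factors cannot be baseline values.

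Three stronger readings are tempting but not supported:

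- *Adjustment wipes out the effect in every comparison.* On the protocol's provider knowledge figures and 10% control rate, arm 2 versus arm 1 cannot lose everything through knowledge. At least about 9 of 15 points remain, and power stays at about 80% or more.
- *Process factors exist only in arms 2 and 3.* The term is not defined. The implementation section also covers RDT distribution and ACT stock-outs, which can occur in all arms. These would absorb less, though they still arise after randomisation.
- *All knowledge is measured after the exit survey.* Only provider knowledge is. Patient knowledge is collected within that survey.

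**Conclusion.** The adjustment rule is wrong as written and should be fixed. The adjusted risk difference does not estimate the effect of the randomised intervention. Bias towards zero is the expected direction under the protocol's own hypotheses, in which the interventions raise knowledge and knowledge improves treatment; it is not a mathematical certainty.

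The size cannot be fixed from the document, because the mediated share is unknown. Under the additive, single-covariate model, the loss is about 2 to 15 of 15 points for arm 3 versus arm 2, and about 1 to 6 of 15 for arm 2 versus arm 1. A process factor found almost only in the intervention arms could absorb nearly everything, but that case rests on an assumed 0% against 90%. A reader should not infer that the main comparison or the sample size is compromised; neither is.

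**What to change.** In Data analysis, limit the stage-1 covariates of the adjusted effect estimate to variables fixed before randomisation or not affected by it: stratum, type and number of facilities, and patient age, sex and socioeconomic status. Remove patient knowledge, provider knowledge and process factors from that model. If they are of interest, analyse them in a separately labelled exploratory mediation or process analysis that is not presented as an adjusted intervention effect. Carry the same restriction into the analysis plan and into the secondary outcomes.

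The cost is a sentence or two and no new data. The change should be made before the data are analysed, because dropping covariates afterwards would look selective.

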### Cost-effectiveness

Cost-effectiveness ratios will be based on the primary outcome (that is the cost per case of suspected malaria that received treatment as recommended in the malaria guidelines) as well as a range of secondary outcomes including changes in provider knowledge. Cost-effectiveness will be calculated for each comparison and will be expressed as incremental cost-effectiveness ratios (ICERs). One-way and multiway sensitivity analysis will be undertaken to examine the effects of varying uncertain variables on study findings. Costs and effects will

be presented in both discounted and undiscounted form.

### Dissemination

Results from the study will be reported at local, national, and international levels. At the local and national level, the Research on the Economics of ACTs (REACT) Project (<http://www.actconsortium.org/pages/project-5.html>) will continue working with the Ministry of Health after the trial is completed to adapt the most cost-effective interventions for national use. At the international level, we also see an opportunity to support the implementation of the 2010 WHO malaria treatment guidelines which acknowledge the need for provider training alongside the large-scale deployment of RDTs and ACTs.

### Trial status

The trial is ongoing. Patients are still being recruited.

### Endnote

aPrices are based on a willingness to pay study undertaken in Enugu State by Uzochukwu *et al.* [38].

### Abbreviations

ACTs: Artemisinin-based combination therapies; RDTs: Rapid diagnostic tests; REACT Project: Research on the economics of artemisinin-based combination therapies.

### Competing interests

The authors declare that they have no competing interests.

# Acknowledgements

Finally, this research is supported by the ACT Consortium, which is funded through a grant from the Bill and Melinda Gates Foundation to the London School of Hygiene and Tropical Medicine. We thank the staff of Enugu State Ministry of Health for their support. We are particularly grateful to the Enugu state Malaria Control Manager, [name] for his very close collaboration with the research team. The authors have no competing interests to declare.

**Submit your next manuscript to BioMed Central and take full advantage of:**

- Convenient online submission
- Thorough peer review
- No space constraints or color figure charges
- Immediate publication on acceptance
- Inclusion in PubMed, CAS, Scopus and Google Scholar
- Research which is freely available for redistribution

Submit your manuscript at  
www.biomedcentral.com/submit

[figure not shown]

Supplement: S1 Protocol — (PDF) [file pone.0133832.s002.pdf]
